**Statistical Analysis**

We will define three groups for analysis:

1. Babies with no markers and no major congenital malformations

2. Babies with a renal marker (PCD, 5 - 9.9mm) on the 18-20 week antenatal ultrasound scan

3. Babies with congenital hydronephrosis (>10mm) on the 18-20 week antenatal ultrasound scan

For groups 2 and 3 we will define three subgroups according to diagnosis at birth:

(a) no pathology (<7 mm)

(b) pelvicalyceal dilatation (7-9.9mm)

(c) confirmed congenital hydronephrosis (>10mm).

We will describe the natural history for babies in groups 2 and 3 including the detail of measurements of PCD at follow-up scans after birth using data from CARIS. We will describe the proportion of babies in sub-groups a, b and c, the proportion of children in these groups with any renal hospital admissions and/or linked procedures, and the incidence of urinary tract infections diagnosed in primary care.

For each baby we will define the length of follow-up and person-years at risk during the five-year study period,

accounting for censoring by death or migration. We will estimate and compare the proportion of hospital

admissions and the person-year incidence of urinary tract infections between groups 1, 2 and 3 according to

maternal age, parity, quintile of Townsend deprivation score quintile, gestational age, sex, and breast-feeding.

We will use time to event Cox’s regression analysis for the first admission to hospital for renal disease to obtain crude and adjusted hazard ratios for groups 2 and 3 as defined above compared to group 1; the adjustments will be for maternal age, parity, social deprivation, gestation, sex, birth-weight and breast-feeding.

We will model the number of urinary tract infections and hospital admissions for renal conditions separately using a negative binomial or Poisson model, depending on whether or not there is over-dispersion, allowing for the varying periods of time at risk for the children in the cohort, adjusting for the factors listed above.

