In Wales, following detection of PCD (5-9.9mm) at the 18–20 week ultrasound scan, a follow-up scan is offered

between 28 – 32 weeks, and if the dilatation is >7 - 8 mm (depending on local protocols) a scan is indicated in

the post-natal period. Congenital hydronephrosis (dilatation > 10mm) detected at the post-natal scan could

indicate VUR and/or obstruction, requiring treatment with prophylactic antibiotics or surgery. Preliminary analysis of data from the Congenital Anomaly Registry and Information Service for Wales (CARIS) showed that 58% of babies with PCD 5-9.9mm detected on antenatal ultrasound scan were followed-up at birth, and of these cases, 28% of babies had congenital hydronephrosis (PCD > 10mm). 80% of babies with congenital hydronephrosis detected on antenatal ultrasound scan (>10mm) were followed up at birth and 77% of these babies had this diagnosis confirmed on post-natal scan. Although congenital hydronephrosis is defined in Europe using the measurement of at least 10mm, local protocols indicate some hospitals use a measurement of at least 7mm to define and treat cases. There are no data on the degree of progression as determined by change in measurement between antenatal or post-natal scan or the influence of measurement error, and no information about the correlation between size of PCD and urinary tract morbidity, so it is not known whether or not the 10mm cut-off to define congenital hydronephrosis is appropriate or not.

One study set in the Netherlands investigated the incidence of urinary tract infections at age 5 – 6 years and

found no difference between babies with and without PCD (5-9.9mm).^20^ However the diagnosis of urinary tract

infection was solely by parental report with no medical diagnosis and so the question remains unanswered. No

study has compared hospital admissions for renal causes between babies with and without PCD.

The natural history and evidence for any association between PCD (5-10mm) and urinary tract outcomes in

childhood needs to be established in order to define clinical guidelines and requirements for subsequent management of pregnancy and postnatal follow-up for this condition.

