**Outcome measures**

1. Proportion of children with any renal hospital admissions (defined by ICD-10 codes N00–N99, Q60-Q64

recorded in the primary or secondary coding position) and/or linked procedures (OPCS-4). We will define the

codes for renal ultrasound scan, micturating cystourethrogram (MCUG), Dimercaptosuccinic (DMSA) scan and

surgery for urinary tract obstruction using the Classification of interventions and procedures (OPCS-4) which is

used for the coding of operations, procedures and interventions performed in the NHS.

2. Incidence of urinary tract infections and repeat infections in children under age five diagnosed in primary care. These will be defined using Read codes for clinical activity and drug prescriptions relating to primary care

diagnosis, investigation and treatment of urinary tract infection. Read codes version 2.0 is available from the

Technology Reference data Update Distribution (TRUD) website, Department of Health, England.

3. Time to first hospital admission for renal conditions in children under age 5 defined by ICD10 codes N00 –

N99 and Q60 – 64 in the primary and secondary coding position. We will code the children who have migrated

out of Wales or who die so that we can take this censoring into account in the analysis.

4. Number of hospital admissions for renal conditions and urinary tract infections (as defined above) during

childhood, over a maximum follow-up period of five years.

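### Subgroups a, b and c are set by a postnatal scan, but their outcomes are not required to start after it, so the classifying scan or admission can count as the subgroup's own outcome

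*Protocol*

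**What the plan says.** In the Protocol, Statistical Analysis, the three main groups are fixed by the 18-20 week antenatal scan. Within the two dilated groups a second split follows: "For groups 2 and 3 we will define three subgroups according to diagnosis at birth", namely below 7 mm (a), 7-9.9 mm (b) and above 10 mm (c). The natural history is to be described "including the detail of measurements of PCD at follow-up scans after birth using data from CARIS". The outcomes by subgroup come next: "We will describe the proportion of babies in sub-groups a, b and c, the proportion of children in these groups with any renal hospital"; that sentence goes on to name admissions, linked procedures and UTI incidence in primary care.

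On time at risk, the same section says "For each baby we will define the length of follow-up and person-years at risk during the five-year study period". The start is not written out. Outcome measures speaks of "Time to first hospital admission for renal conditions in children under age 5", and Sample size calculations gives risks by the first, fourth and fifth birthdays, so a start at birth is implied.

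Outcome measures, item 1, covers any renal admission coded N00-N99 or Q60-Q64 and/or linked procedures, and names renal ultrasound among the procedures to be coded. Sample size calculations lists hydronephrosis (N13.3) among the commonest reasons for renal admission under age five.

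Background reports that "58% of babies with PCD 5-9.9mm detected on antenatal ultrasound scan were followed-up at birth", and that 28% of those had hydronephrosis. The trigger it gives for a postnatal scan is the size found at a repeat antenatal examination: "between 28 – 32 weeks, and if the dilatation is >7 - 8 mm (depending on local protocols) a scan is indicated in", where that sentence then names the period after birth.

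**The concern.** A size in millimetres after birth is known only once a postnatal scan has been done. If outcomes run from birth and the scan may come at any later time, a baby can have the outcome before, or on the same occasion as, being classified. Two routes follow.

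1. The classifying event is itself an outcome. An admission at which hydronephrosis is found and coded N13.3 both puts the baby in c and counts as a renal admission in c. A classifying renal ultrasound, if recorded as a linked procedure, meets outcome 1 directly; if that happened for every classified baby, the combined admission-or-procedure proportion would be 100% by construction.
2. An event leads to the scan. A baby not scanned at birth who is later imaged because of an infection or admission could be placed in b or c by that scan, and the event credited to the subgroup.

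The a/b/c description is the only planned analysis of postnatal size against later morbidity. Background says it is not known whether the 10 mm cut-off is appropriate, and Expected outputs directs the findings to guidelines and care pathways. Both routes can make subgroup c look worse than it is; the second also makes unscanned babies look better.

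**Working it through.** The Protocol gives no figure for this point, so there is none to reproduce.

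**Passages side by side**

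| Element | What the Protocol fixes |
|---|---|
| Subgroup label | Diagnosis at birth, by size in mm |
| Source of postnatal measurements | CARIS, follow-up scans after birth; no window, no rule for several scans |
| Babies without a postnatal scan | No category |
| Subgroup outcomes | Renal admissions, linked procedures, UTI incidence |
| Period | Five years, under age 5; no restart at the scan |
| Outcome codes | Include N13.3 (within N00-N99) and renal ultrasound |

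Nothing here makes classification precede the outcome, so route 1 follows from the text. One limit applies: Data sources describes the hospital dataset as admissions data, so a scan counts only where it is recorded there as a linked procedure. The Protocol does not say how often that is.

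**Illustration of route 2**

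Inputs from the Protocol: 148 children with PCD (Sample size calculations); 58% followed up at birth and 28% of those above 10 mm (Background); background renal admission risk by the fifth birthday p = 3.3% (Sample size calculations).

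Assumptions: no true link between size and events; a fraction q of events in babies not followed up prompts a scan; h = 28% of those scans show more than 10 mm. The Protocol gives no value for q, and h is borrowed from the babies who were followed up.

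- Followed up at birth: 148 x 0.58 = 85.8. Not followed up: 148 x 0.42 = 62.2.
- Subgroup c from scans at birth: 85.8 x 0.28 = 24.0.
- Expected admissions by age five: 24.0 x 0.033 = 0.8 in c; 62.2 x 0.033 = 2.1 in those not followed up.
- Babies moved into c, each with an event: 62.2 x p x q x h. At q = 1 this is 2.05 x 0.28 = 0.57.
- Apparent risk in c = (24.0p + 62.2pqh) / (24.0 + 62.2pqh).

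| q | Babies moved | Apparent risk in c | Ratio to true | Risk left in unscanned |
|---|---|---|---|---|
| 0 | 0 | 3.3% | 1.00 | 3.3% |
| 0.25 | 0.14 | 3.9% | 1.17 | 2.5% |
| 0.5 | 0.29 | 4.4% | 1.35 | 1.7% |
| 1 | 0.57 | 5.6% | 1.68 | 0% |

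For q = 1: (0.793 + 0.574) / (24.04 + 0.574) = 1.367 / 24.61 = 5.6%.

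**Higher risk.** If PCD carried the hazard ratio of 3.5 by the fourth birthday named in the power statement, risk would be 1 - (1 - 0.028)^3.5 = 9.5%. Subgroup c would then read 12.5% (q = 0.5) or 15.3% (q = 1), with at most 62.2 x 0.0946 x 0.28 = 1.6 babies moved.

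UTIs cannot be sized, because no primary-care rate is given. Nor can group 3: 20% were not followed up at birth, but its number of babies is not stated.

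**The case against.** The strongest reply is that the Protocol says diagnosis at birth and means it. On that reading a, b and c classify only babies scanned around birth, the sentence on follow-up scans merely describes later measurements, and the remaining 42% have no subgroup. The documented trigger for a postnatal scan is the 28-32 week measurement, which no infection or admission after birth can cause. The subgroups are only described, the start of follow-up is not written out, and scan windows are often left to an analysis plan, which is not shown here.

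Much of this stands. A reader might infer that the plan assigns subgroups from scans prompted by a UTI or admission. No passage says so; the Protocol only fails to exclude it. A reader might also infer that the main hazard ratios are biased. They are not exposed: the Cox model gives "crude and adjusted hazard ratios for groups 2 and 3 as defined above compared to group 1", and those groups are fixed before birth, as they are for the count models.

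A larger size is also tempting: suppose 2 of the 24 babies in c were scanned because of an event, giving 2/24 = 8 percentage points. That is unsound. The 24 all come from the 58% followed up at birth, while the mechanism concerns the other 42%. Moving 2 babies into c would need 2/0.28 = about 7 event-prompted scans among 62, and nothing in the Protocol supports that rate.

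The objection does not dispose of the central point. Even on the narrow reading, a scan at birth comes after the implied start of follow-up, and it or the admission around it falls within the outcome codes. The Protocol itself fixes the label, the outcomes and the period in a way that lets them overlap, so this is more than detail left for later.

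**Conclusion.** The point holds for the descriptive a/b/c results only. As written, the scan or hydronephrosis admission that assigns the subgroup can be counted as that subgroup's outcome. Assignment by a later, event-prompted scan is an open risk, not a stated feature of the plan.

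For the second route, the illustration gives an apparent risk in c of 4.4% to 5.6% against a true 3.3%, a ratio of about 1.3 to 1.7, for q between one half and one. It rests on assumed q and h, on no true size effect and on follow-up from birth, and it moves less than one expected baby at background risk. In absolute terms the effect is small, but c has only about 24 babies and 0.8 expected admissions, so a single misattributed event would be visible. The first route cannot be sized from the Protocol. The change is worth making before analysis; it does not threaten the main comparison.

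**What to change.** In Statistical Analysis:

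- State which early postnatal scan defines a, b and c, and the time window in which it must fall. This is a rule for the analysis and asks for no change in who is scanned or when.
- Count subgroup outcomes and person-time only after that scan or the end of the window, and exclude the classifying scan and its admission from the outcomes.
- Report as separate rows the babies with no scan in the window and those first scanned after a renal admission or UTI.

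In the illustration this restores the q = 0 row: the apparent risk in c equals the true risk.

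The cost is wording plus scan and event dates. That CARIS can supply scan dates is an assumption; Data sources does not say so. Some early-infancy events leave the subgroup table, including events in babies whose scan was already indicated before birth, so these should be listed separately. The proportions in a, b and c may also shift, since late-scanned babies no longer enter them. The Cox and count models for groups 1 to 3 stay as they are.

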**Study Design and Method**

**Study population and method**

This study will include babies born in Wales between 1st January 2009 and 31st December 2011 to mothers who consented to take part in the WSMB. All pregnant women receiving antenatal care in NHS Wales who had a mid pregnancy fetal anomaly scan provided by the NHS in Wales between 1st July 2008 – 31st March 2011 were eligible for recruitment to the study. Scan data were available for 74% of women in the study who had

singleton pregnancies (n=22,045). The maximum period of follow-up in this study will be five years, accounting for censoring by death or migration.

We will describe the natural history of PCD (5-9.9mm) and compare the pattern of hospital admissions for renal causes (using ICD10 codes N00–N99, Q60-Q64), interventions and procedures due to renal causes (using OPCS-4 codes), and the incidence of urinary tract infection (using Read codes) during childhood, in those with and without markers.

In order to carry out the analysis we will record link the babies in the WSMB to hospital admissions data and primary care data from general practices, with anonymised linkage of individual babies across the

datasets. This data linkage will be done by HIRU at Swansea University, using the SAIL databank.^21,22^ The data

contained within the databank are sensitive and HIRU have developed procedures to ensure the data is made

available for research whilst ensuring that individual confidentiality is protected, and have measures in place to ensure information governance standards are met.

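### Outcome 1 is a proportion with no stated age, although follow-up varies between children; taken as a plain proportion it understates the absolute risk by any given age

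*Protocol*

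**What the plan says.** Protocol, Outcome measures, item 1: "Proportion of children with any renal hospital admissions", by ICD-10 code, and/or linked procedures by OPCS-4 code. No age or time horizon is attached. Items 2 and 3 are limited to children under five, and item 4 to a maximum of five years.

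Protocol, Study population and method: "The maximum period of follow-up in this study will be five years, accounting for censoring by death or migration".

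Protocol, Statistical Analysis, in order:
- For the birth-diagnosis subgroups (a) to (c) of groups 2 and 3, the proportion with any admission and/or linked procedure will be described.
- Time at risk is then set out child by child: "For each baby we will define the length of follow-up and person-years at risk during the five-year study period". The sentence ends by saying that death and migration are allowed for as censoring.
- The group comparison follows. For admissions the wording is "We will estimate and compare the proportion of hospital", completed by the word for admissions. Infection is given a different measure in the same sentence, namely "the person-year incidence of urinary tract infections between groups 1, 2 and 3". Both are to be broken down by maternal age, parity, deprivation, gestational age, sex and breast-feeding.
- Cox regression for first renal admission gives hazard ratios. Poisson or negative binomial models for the numbers of infections and admissions allow for time at risk.

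Outcome measures, item 3 (time to first admission), is the only outcome whose definition mentions censoring: children will be coded who have migrated "out of Wales or who die so that we can take this censoring into account in the analysis".

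**The concern.** The sentence that compares the groups gives urinary tract infection a person-time denominator and gives admissions a proportion. Nothing in the section names a fixed age, a cumulative-incidence estimate or a restriction to fully followed children for that proportion. Followed as written, its denominator is all children in the group, including those who left Wales after one or two years.

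Such a figure is the risk over whatever follow-up happened to be available, not the risk by age five. It would not be comparable with the by-birthday risks in Sample size calculations, and two strata with the same true risk but different out-migration would give different figures. The Cox and count models do not supply what is missing, because they yield ratios and not an absolute risk by a given age. Absolute risk matters here: the Protocol justifies the study largely as natural history, and Expected outputs of research says the findings will be used to inform parents.

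**Working it through.** The Protocol gives no expected value for outcome 1, so there is no figure of its own to reproduce. The check asks how far a plain proportion would fall below the five-year risk.

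**Inputs from the Protocol.** Background risk of renal admission: 1% by the first birthday, 2.8% by the fourth, 3.3% by the fifth (Sample size calculations). Births: 1 January 2009 to 31 December 2011 (Study population and method).

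**Assumptions, none of them in the Protocol.** Risk rises linearly between the stated birthdays: 1.0 percentage point in year 1, (2.8 − 1.0)/3 = 0.6 points a year in years 2 to 4, and 0.5 points in year 5. Migration occurs at a constant rate *c* per year, unrelated to admission. Data end dates are varied.

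**A. Migration only; every child could reach age five.** A child counts as admitted only if still in Wales at the time, so

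plain proportion = [0.010(1 − e^−c) + 0.006(e^−c − e^−4c) + 0.005(e^−4c − e^−5c)] / c

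- c = 0.02: 0.010 × 0.9901 + 0.006 × 2.8541 + 0.005 × 0.9139 = 0.0316, or 3.16%. 3.16/3.30 = 0.957, about 4% too low.
- c = 0.04: 0.010 × 0.9803 + 0.006 × 2.7161 + 0.005 × 0.8353 = 0.0303, or 3.03%. 3.03/3.30 = 0.917, about 8% too low.
- c = 0: 3.30%, no understatement.

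**B. Data end before every child reaches five; no migration.** Births spread evenly over 2009–2011. Interpolated risks are 1.6% at age 2, 2.2% at 3, 2.8% at 4 and 3.3% at 5. The average for each birth year is the midpoint of the risks at the youngest and oldest age reached.

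| Data end on | Born 2009 | Born 2010 | Born 2011 | Mean | Relative to 3.3% |
|---|---|---|---|---|---|
| 1 Jan 2017 | 3.30 | 3.30 | 3.30 | 3.30% | none |
| 1 Jan 2016 | 3.30 | 3.30 | 3.05 | 3.22% | 2.5% low |
| 1 Jan 2015 | 3.30 | 3.05 | 2.50 | 2.95% | 11% low |
| 1 Jan 2014 | 3.05 | 2.50 | 1.90 | 2.48% | 25% low |

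**C. Effect on the group comparison.** Take a true hazard ratio of 3.5, so the five-year risk in group 2 is 1 − (1 − 0.033)^3.5 = 11.08%, and the true risk ratio is 11.08/3.30 = 3.36. If 20% of each group is lost by age five, the plain proportions are 10.08% and 3.00%, and the ratio is again 3.36. If there is no true effect but 10% of group 1 and 20% of group 2 are lost, the proportions are 3.15% and 3.00%, and the ratio is 3.00/3.15 = 0.95 instead of 1. The same arithmetic applies to two covariate strata with unequal loss.

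**D. Death.** A child who dies without an admission never will have one, so counting that child as not admitted is right for cumulative incidence. Only migration, and any end of data, produce the understatement.

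**The case against.** The Protocol does not call this proportion crude; it uses that word only for hazard ratios. The sentence just before the comparison says censoring by death or migration is accounted for, and the estimator could be settled in a statistical analysis plan that is not shown. This stands in part: the text is ambiguous and does not fix a crude estimator. But that clause qualifies length of follow-up and person-years, and a plain proportion uses neither. The Protocol itself chooses the summary measure and leaves it without an age.

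A reader might infer that the reported risks will be too low by a definite and sizeable amount. The documents do not support that. They name only death and migration as censoring, and give neither a migration rate nor a data end date. The larger shortfalls in table B rest wholly on assumed end dates, and with complete follow-up there is no shortfall.

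A reader might also infer that the comparison between groups is compromised. For admissions it is covered by the Cox and count models, which handle unequal follow-up, and part C shows that even the ratio of plain proportions hardly moves under equal loss. Nothing in the Protocol shows that loss differs between groups or strata.

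Sampling error in the group of interest is also far larger than the shift. With 148 children with pelvicalyceal dilatation, 5 events (3.4%) would have a 95% Wilson interval of about 1.5% to 7.7%. That is true, but it does not excuse a systematic understatement, and it does not apply in the same way to the large comparison group.

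**Conclusion.** The point holds in a limited, conditional form. Outcome 1 has no age horizon, and the Protocol does not say how unequal follow-up enters the proportion. If it is taken as a plain proportion, it understates the absolute risk by a given age wherever follow-up is incomplete because of migration or end of data.

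The amount is not knowable from the Protocol. It is about 4–8% in relative terms (0.14 to 0.27 percentage points on 3.3%) if every child could reach age five and 2–4% a year migrate, both assumed, and more if data end before all children reach five. The harm is to the absolute risks in groups, subgroups and strata, and to comparisons of strata with different loss. Hazard and rate ratios for admissions are little affected. This is worth correcting before analysis, but it does not threaten the study's main group comparisons.

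**What to change.** Define outcome 1 as the cumulative incidence of the first event by stated birthdays, for example the first, fourth and fifth, which are the ages used in Sample size calculations. Give it for renal admission alone, which is comparable in definition with the planning risks, and for the full composite with linked procedures, so that no part of the present outcome is dropped. Treat migration and any end of data as censoring, and death as a competing event; a plain Kaplan–Meier estimate would treat death as censoring. Report 95% confidence intervals for groups 1 to 3 and for the covariate strata, and use the same estimate when describing subgroups (a) to (c). State the data end date.

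The cost is small. Dates of first admission, migration and death are already needed for the Cox model. The one additional step is to derive a first-event date for the linked procedures, which outcome 3 does not include.

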**Project summary**

Long term kidney disease is one of the most common illnesses of childhood causing lifelong health needs. Babies born with abnormalities in the kidney are at risk of long-term kidney disease that may require

treatment such as dialysis and kidney transplant as they grow older. Opportunities for early diagnosis and treatment of kidney disease may reduce the severity of illness over time. In some pregnancies the marker pelvicalyceal dilatation, is detected in the baby’s kidney at the antenatal ultrasound scan. The meaning of this marker for the future health of the baby (for example the risk of urine infections or hospital admissions for kidney problems) is not known. There are no consistent guidelines about how to treat babies with this condition and so the identification of this marker can lead to anxiety for families and additional tests during pregnancy and after birth. We were funded by NISCHR to study the meaning of markers of uncertain significance (Welsh Study of Mothers and Babies). The study has recruited 21,106 pregnant women, with consent to follow-up the babies in future studies. There are 150 babies in our study with the kidney marker. We did not find any associations with immediate birth outcomes such as stillbirth, premature birth or genetic problems.

We propose a prospective electronic cohort study in which we will record link the data on babies already

recruited to the Welsh Study of Mothers and Babies (WSMB) with routinely collected health care datasets in

Wales to obtain follow-up data on hospital admissions and diagnoses in primary care during childhood. We will

describe the natural history of pelvicalyceal dilatation (5-9.9mm – PCD) and compare the pattern of hospital

admissions, interventions and procedures due to renal causes and the incidence of urinary tract infection during childhood between:

1. Babies with no markers and no major congenital malformations

2. Babies with a renal marker (PCD, 5 - 9.9mm) on the 18-20 week antenatal ultrasound scan

3. Babies with congenital hydronephrosis (>10mm) on the 18-20 week antenatal ultrasound scan

The information obtained will play an important role in facilitating the development of appropriate clinical guidelines and care pathways during pregnancy and after birth, including the appropriate use of medical interventions and treatment. We plan to publish results in peer review journals.

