**Sample size calculations**

Prelimiunary data from the PEDW dataset for the period 1998 to 2008 linked to 329,000 live births from WECC,

showed that there was a 1% chance of a renal admission before the first birthday, increasing to 2.8% by the

fourth birthday and 3.3% by the fifth birthday. The most common reasons for renal admission in children under 5 were urinary tract infection (ICD10 N39.0), non-specific renal condition (ICD10 39.9) and hydronephrosis (ICD10 N13.3). Admissions were more common in boys than girls, with a relative risk ratio of approximately 1.6. We will compare the rates of renal admissions between the 148 children with PCD and those without a marker. There will be 80% power for detecting a hazard ratio of at least 6.2 in admissions by the first birthday and for detecting a hazard ratio of 3.5 by the fourth birthday. Whilst these are large effect-sizes this study presents a unique opportunity to describe the natural histrory of PCD.

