**Expected outputs of research**

The potential for maternal anxiety and difficulty in counselling women when markers are reported and the need for a consistent approach in the management of pelvicalyceal dilatation (PCD) is the principlal reason for this research. The impact of this work will be significant as information about the significance of renal ultrasound markers is not currently available. This work will address current gaps in the evidence-base about the health outcomes in infancy and childhood associated with renal pelvicalyceal dilatation. The findings from the study will further our understanding of the natural history of PCD and contribute significantly to the development of evidence-based clinical guidelines and care-pathways for the management of this condition. The findings will be used to provide accurate information for parents and avoid any unnecessary anxiety during pregnancy. Determination of the significance of this marker will also enable future cost-benefit analyses of reporting this marker and the utility of the marker in predicting health outcomes in children.

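### The only adjustment set mixes factors fixed by the 18–20 week scan with birth and feeding factors that follow it, so no jointly adjusted estimate matches the stated use in pregnancy

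*Protocol*

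**What the plan says.** The Statistical Analysis section defines the groups by the antenatal scan. Group 2, for example, is "Babies with a renal marker (PCD, 5 - 9.9mm) on the 18-20 week antenatal ultrasound scan". Group 3 is defined at the same scan.

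For time to first renal admission, the section plans a Cox model giving "crude and adjusted hazard ratios for groups 2 and 3 as defined above compared to group 1". For the adjusted version, "the adjustments will be for maternal age, parity, social deprivation, gestation, sex, birth-weight and breast-feeding". The numbers of urinary tract infections and of renal admissions are each modelled by Poisson or negative binomial regression, "adjusting for the factors listed above". One list therefore serves all three models. The section also plans to compare admission proportions and infection incidence between groups by level of several listed characteristics, sex and deprivation among them.

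On purpose, the Expected outputs section says "The findings will be used to provide accurate information for parents and avoid any unnecessary anxiety during pregnancy". It also looks ahead to work on "the utility of the marker in predicting health outcomes in children". The protocol states no aim of separating a direct effect of the scan finding from an effect through birth factors.

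**The concern.** A parent counselled after the scan, or a clinician judging the marker as a predictor, knows maternal age, parity, deprivation and possibly fetal sex. Neither knows the baby's birth-weight, gestation at delivery or feeding. A hazard ratio that holds those equal answers a different question: how much association remains among babies with the same birth and feeding characteristics.

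If the later factors carry part of the association, the adjusted ratio leaves that part out. The protocol's own Background makes such routes plausible: reporting a marker can cause anxiety and lead to invasive tests and further scans, and PCD babies are offered a later antenatal scan and, depending on size, a postnatal one.

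At stake is whether the study reports a jointly adjusted estimate that matches its stated use. As planned, the reader has a crude ratio without confounder control and an adjusted ratio that conditions on later events.

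**Working it through.** **Timing of each listed factor, set against exposure at 18–20 weeks**

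- Fixed by the scan: maternal age, parity, social deprivation, sex.
- After the scan: birth-weight, breast-feeding.
- Undefined: gestation. Gestation at the scan is almost constant by design, and the same section lists gestational age beside sex and breast-feeding as a characteristic of the baby. Gestation at birth is the sensible reading.

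No planned multivariable model contains the first group alone.

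**Does the rest of the plan fill the gap?**

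The crude hazard ratio does not condition on later factors, but it leaves sex uncontrolled. The Sample size calculations section puts renal admissions in boys against girls "with a relative risk ratio of approximately 1.6". The mean hazard in a group with a proportion *p* of boys is proportional to 1 + 0.6*p*. Assume 51% boys among unexposed babies and 60–70% among exposed babies (neither figure is in the protocol):

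- 60%: (1 + 0.6 × 0.60)/(1 + 0.6 × 0.51) = 1.36/1.306 = 1.04
- 70%: (1 + 0.6 × 0.70)/(1 + 0.6 × 0.51) = 1.42/1.306 = 1.09

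On those assumptions the crude ratio would be inflated by 4–9% through sex alone. The descriptive comparisons, read one factor at a time, do not control the pre-scan factors jointly either.

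**How much could conditioning on a later factor matter?**

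The protocol gives no figure for this, so there is none to reproduce. Take one binary factor with prevalence *p*e in exposed and *p*u in unexposed babies, which multiplies the hazard by *r*. Conditioning on it removes approximately the factor (1 + *p*e(*r* − 1))/(1 + *p*u(*r* − 1)). With preterm birth as the factor, *r* = 2 and *p*u = 7% (all assumed):

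- Group 2, *p*e = 10.5%: 1.105/1.07 = 1.033. About 3% of the ratio is removed.
- Group 3, *p*e = 20%: 1.20/1.07 = 1.12. Since 1 − 1/1.12 = 0.11, about 11% of the ratio is removed.

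Over a wider assumed range (*p*u = 6%, *p*e = 10–20%, *r* = 1.2–3):

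- Lowest: (1 + 0.10 × 0.2)/(1 + 0.06 × 0.2) = 1.02/1.012 = 1.01
- Highest: (1 + 0.20 × 2)/(1 + 0.06 × 2) = 1.40/1.12 = 1.25

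If the marker is unrelated to the factor, the result is 1. If the factor is rarer in exposed babies, the shift reverses.

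**What does the reported null for prematurity exclude?**

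The Project summary says of the marker babies: "We did not find any associations with immediate birth outcomes such as stillbirth, premature birth or genetic problems". With 150 babies and an assumed 7% preterm rate, 150 × 0.07 = 10.5 preterm births are expected. An approximate 95% range for the preterm ratio around 1 is exp(±1.96 × √(1/10.5)), or 0.55 to 1.8. The 10.5% used above for group 2 is a ratio of 1.5, inside that range.

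**The case against.** The strongest reply is that the effect is too small to matter. For group 2, the group the study is sized for, the illustration gives about 3%, and the protocol reports no association with premature birth. At the hazard ratio of 3.5 quoted for the fourth birthday, about 148 × 0.028 × 3.5 = 14.5 exposed events are expected. The 95% limits are then roughly the estimate multiplied or divided by exp(1.96/√14.5) = 1.67, ignoring the small contribution from group 1. A 3% shift is lost in that. This stands as a limit on size. It does not settle the matter for group 3, birth-weight or breast-feeding, which the reported null does not mention.

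A second reply is that the results also serve care after birth, as the Project summary and Background say. Gestation and birth-weight are then known, so an association beyond birth factors is a fair question. That stands, and is a reason to keep the planned model, though not as the only adjusted one.

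A third is that the crude ratio and absolute risks by group already serve counselling. They do in part, but without joint control of the pre-scan factors.

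A reader might go further and infer that these later factors can only be mediators or colliders. That is too absolute: they may partly stand in for unmeasured pre-scan factors, such as social circumstances that an area deprivation score captures poorly, and adjustment could then reduce confounding. A reader might also infer that children with missing feeding data will be dropped, or that an admission may alter the feeding record. The protocol states no complete-case rule and does not say when breast-feeding is recorded, so neither inference is supported.

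**Conclusion.** The concern holds as a mismatch between the estimate and its stated use. The single adjustment set, shared by the Cox model and both count models, includes factors that arise after the exposure is defined, and no planned model adjusts jointly for the pre-scan factors alone. This rests on reading gestation as gestation at birth; birth-weight and breast-feeding make the point without it.

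The documents show neither the size nor the direction of the difference. On the assumed inputs it is probably small for group 2 and could be larger for group 3. A reader might infer that the adjusted ratios will be seriously biased; the protocol does not support that. The change is worth making because it is cheap and supplies the estimate that the Expected outputs section calls for.

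**What to change.** In the Statistical Analysis section:

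1. Make the main adjusted Cox and count models adjust for maternal age, parity, deprivation and sex.
2. Report the model with the full current list as secondary, labelled as conditional on birth and feeding factors.
3. Define gestation.

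This takes a sentence or two and one extra results column. It needs no new data and removes nothing planned. The downside is one more adjusted estimate per outcome, which is why the main one should be named in advance.
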